# Early Detection of Type 1 Diabetes in First-Degree Relatives in Saudi Arabia (VISION-T1D): Protocol for a Pilot Implementation Study

**DOI:** 10.2196/70575

**Published:** 2025-04-14

**Keywords:** islet autoimmunity, type 1 diabetes mellitus, T1D, screening program, antibody detection by agglutination–polymerase chain reaction, PCR, ADAP, human leukocyte antigen, genetic risk score

## Abstract

**Background:**

Type 1 diabetes (T1D) is a growing global health concern, with a notable rise in incidence in Saudi Arabia. Despite the potential benefits of early detection through screening programs, such initiatives are currently lacking in Saudi Arabia and other Arab countries.

**Objective:**

This study aims to evaluate the feasibility, acceptability, and cost-effectiveness of a T1D-screening program targeting high-risk individuals, specifically children with a first-degree relative diagnosed with T1D.

**Methods:**

The VISION-T1D program is a prospective cohort study focused on the early detection of presymptomatic T1D by screening children aged 2-18 years. The primary screening method involves testing for islet autoantibodies, including insulin autoantibodies, glutamic acid decarboxylase autoantibodies, insulinoma associated-2 autoantibodies, and zinc transporter-8 autoantibodies. Optional genetic testing, including human leukocyte antigen phenotyping and the genetic risk score, is offered. Outcomes include the feasibility of the screening process, prevalence of early-stage T1D, psychological impacts, educational intervention effectiveness, progression rates to stage-3 T1D, and economic viability.

**Results:**

The VISION-T1D program began in May 2024. As of December 2024, a total of 176 families have been enrolled. Data collection will continue until April 2025, with final data analysis projected for mid-2025.

**Conclusions:**

The VISION-T1D study provides a practical approach to T1D screening tailored to the health care landscape of Saudi Arabia. The insights gained from this pilot program will inform the development of a national, population-based screening initiative designed to reduce diabetic ketoacidosis at diagnosis, improve long-term outcomes, and alleviate the economic burden of T1D. The VISION-T1D initiative could also serve as a scalable and sustainable model that can be adopted internationally, contributing to global efforts to manage and prevent T1D.

**Trial Registration:**

ClinicalTrials.gov NCT06513247; https://clinicaltrials.gov/study/NCT06513247

**International Registered Report Identifier (IRRID):**

DERR1-10.2196/70575

## Introduction

### Background

The incidence of type 1 diabetes (T1D) is rising globally, with Saudi Arabia reporting a surge to 31.4 per 100,000 youths annually, making a nearly 9-fold increase over the past decade [1,2]. This trend is compounded by high rates of diabetic ketoacidosis (DKA) at diagnosis [3], ranging from 40% to 77%, the highest in the Arab region [4,5]. DKA at T1D onset is associated with significant morbidity, mortality, and long-term complications [6-9]. DKA also imposes a substantial economic burden through direct and indirect medical costs [10-12]. Early detection by T1D screening is crucial in reducing DKA incidence and mitigating the health and economic impacts [13,14].

T1D pathogenesis involves a complex interplay of genetic predisposition and environmental factors, resulting in the autoimmune destruction of pancreatic β-cells [15,16]. Individuals with a first-degree relative (FDR) affected with T1D have a 15-fold higher lifetime risk of developing T1D compared to the general population [13]. Screening for islet autoantibodies identifies presymptomatic stages (stages 1 and 2) at least in children, adolescents, and young people, enabling timely interventions that may alter disease progression [13,17-19]. Individuals with multiple positive islet autoantibodies have a 99% lifetime risk of progressing to clinical stage-3 T1D, with 84% developing insulin-dependent diabetes within 15 years of seroconversion [18-20]. Screening programs in several countries have successfully reduced DKA at diagnosis, improved long-term outcomes, and lowered health care costs [13,14].

Despite successful screening initiatives in other countries, Saudi Arabia and neighboring Arab countries lack such programs. Moreover, most prior efforts have been confined to research settings, leaving a gap in knowledge about real-world implementation in health care settings [14,18,20,21]. The VISION-T1D protocol (NCT06513247) aims to bridge this gap by evaluating the feasibility and cost-effectiveness of a pilot, T1D-screening program for FDRs of individuals with T1D in Saudi Arabia. Aligned with Saudi Arabia’s National 2030 Vision, which prioritizes health improvement and the reduction of chronic disease burden, the VISION-T1D initiative aims to establish a robust framework for broader, population-based, T1D-screening implementation in Saudi Arabia. Furthermore, it could also serve as a scalable and sustainable model for international adoption, thereby contributing to global efforts to manage and prevent T1D.

### Study Objectives

#### Primary Objectives

The primary objectives are as follows:

Evaluate the feasibility of implementing a pilot, T1D-screening program for early detection in FDRs of patients with T1D in Saudi Arabia.Determine the prevalence of stages-1, -2, and -3 T1D among FDRs of patients with TID in Saudi Arabia.

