## Methods

### Study Design and Setting

The Vision-T1D study is a prospective cohort designed to screen children aged 2-18 years who have an FDR with T1D (index case). Participants are recruited from the University Diabetes Centre (UDC) at King Saud University Medical City (KSUMC) in Riyadh, Saudi Arabia. The diagnosis of T1D in index cases is based on the American Diabetes Association criteria [22], and T1D classification is determined by a clinical diagnosis from a specialized endocrinologist, with or without confirmatory islet autoantibodies testing. Exclusion criteria included index cases diagnosed with other forms of diabetes and non-Saudi children due to different ethnic and genetic backgrounds.

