### Phase 1: T1D-Screening Procedures and Data Collection

#### Recruitment and Enrollment

Active and passive recruitment strategies are used. Research staff identified potential participants by reviewing patient lists from KSUMC diabetes clinics and pediatric endocrinology inpatient records. Recruitment materials, including advertisements with QR codes, are shared via the UDC and on social media platforms. The QR codes were linked to an introductory video explaining the study and eligibility criteria, along with a contact submission form. Families who decline participation are asked about the reason for refusal.

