### Statistical Analyses

#### Sample Size

The target enrollment is 1300 participants (or 322 families), based on the feasibility of recruiting 70% of eligible families from the UDC clinic cohort. The estimated seropositivity rate for islet autoantibodies among children with an FDR diagnosed with T1D is estimated at 5% to 15%, with a 90% significance level and 80% power. Considering that the UDC serves approximately 450-500 children with T1D, and that the typical Saudi family has 4-6 children younger than the age of 18 years, this sample size is calculated to be sufficient. Recruitment will be expanded to FDRs outside the UDC cohort if the family target is met without reaching the participant’s goal.

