#### Statistical Analysis

Descriptive statistics will report continuous data as mean (SD) for normally distributed variables and categorical data as frequency and percentage (N, %). Feasibility metrics and T1D stages will also be summarized as percentages.

To evaluate the psychological effects of T1D screening on caregivers, pre- and postscreening levels of anxiety, depression, and distress will be compared using paired 2-tailed *t* tests or Wilcoxon signed-rank tests, depending on data distribution. The effectiveness of educational counseling will be analyzed similarly, comparing pre- and postintervention test scores. Longitudinal changes in the psychological measures will be evaluated using repeated-measures ANOVA or mixed effects models to track patterns over time.

For participants with presymptomatic T1D, progression rates to stage 3 will be analyzed using Kaplan-Meier survival analysis. Time to event will be calculated from screening age to age at stage-3 T1D diagnosis or last follow-up. Cox proportional hazards models will assess factors associated with disease progression, such as baseline autoantibody titers, genetic risk scores, and demographic variables.

At the 1-year follow-up, cost-effectiveness will be assessed by reporting total costs for all screened participants, cost per child screened, and cost per case detected. The incremental cost-effectiveness ratio calculations will compare outcomes for screened children with controls diagnosed with stage-3 T1D in the general population. The incremental cost-effectiveness ratio will incorporate potential benefits, such as reduced DKA incidence and improved HbA_1c_ levels, while adjusting for control characteristics like age and FDR status.

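### The primary prevalence objective is worded for relatives across Saudi Arabia, but the design samples Saudi children reached through one Riyadh centre, partly by self-referral, and the limitations do not say so

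*Protocol article*

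**What the plan says.** The Primary Objectives section sets the target: "Determine the prevalence of stages-1, -2, and -3 T1D among FDRs of patients with TID in Saudi Arabia". The Methods describe a narrower group:

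- **Setting.** "Participants are recruited from the University Diabetes Centre (UDC) at King Saud University Medical City (KSUMC) in Riyadh, Saudi Arabia" (Study Design and Setting). The same section restricts screening to ages 2-18.
- **Exclusions.** "Exclusion criteria included index cases diagnosed with other forms of diabetes and non-Saudi children due to different ethnic and genetic backgrounds" (same section).
- **Active route.** "Research staff identified potential participants by reviewing patient lists from KSUMC diabetes clinics and pediatric endocrinology inpatient records" (Recruitment and Enrollment).
- **Self-referral route.** "Recruitment materials, including advertisements with QR codes, are shared via the UDC and on social media platforms" (same section). The codes lead to a contact form. No condition is attached to this route.
- **Outside families.** "Recruitment will be expanded to FDRs outside the UDC cohort" (Sample Size), but only if 322 families are reached and 1300 participants are not.
- **Analysis.** "Feasibility metrics and T1D stages will also be summarized as percentages" (Statistical Analysis). No split by route is stated.

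The generalizability caveat in the Discussion compares first-degree relatives with the wider population. The Discussion also lists the combination of recruitment strategies among the measures that deal with generalizability.

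**The concern.** Stage prevalence is a primary result, and the article says the findings will inform a national programme and health policy. A reader who takes the objective at its word will read the percentage as a national figure for relatives. The sample contains no adult relatives and no non-Saudi residents, and it has no sampling frame beyond one centre.

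It also mixes two kinds of family: those invited from a list and those who came forward. Families may come forward for reasons related to the outcome. If they do, the pooled percentage depends on the mix of routes as well as on disease, and a larger sample does not remove that dependence.

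Stage 3 is the most exposed. Under Clinical T1D Screening, children with reported symptoms have HbA1c and glucose tested at enrollment and may be found to have stage 3 disease. The outcome definition of stage 3 admits children with one autoantibody, but under Monitoring for Single Autoantibody Results such children have a metabolic assessment only if symptoms develop. For them, detection of stage 3 depends on symptoms. If symptoms also prompt self-referral, selection and detection would push in the same direction.

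**Working it through.** **1. What the sample size rests on.** Inputs from Sample Size: 70% recruitment, 450-500 children with T1D at the centre, 4-6 children per family, targets of 322 families and 1300 participants.

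- 322 / 0.70 = 460 families, which lies inside 450-500.
- 322 x 4 = 1288, against the stated 1300 (12 short, 0.9%).

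The target is thus reproduced from what one centre can supply. No national frame enters it.

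**2. How many participants could come from outside.** With k eligible children per family, the outside share is 1 - 322k/1300, or zero if negative.

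| k | From 322 families | Outside share |
|---|---|---|
| 3 | 966 | 334/1300 = 26% |
| 3.5 | 1127 | 173/1300 = 13% |
| 4 | 1288 | 12/1300 = 1% |
| 5 | 1610 | 0% |

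On the protocol's own 4-6 children the outside share is 0-1%. The 26% needs an added assumption: that the index child is counted among the four, leaving three to screen.

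**3. Effect of mixing routes.** Let f be the share of self-referred (and any outside) children and RR their prevalence relative to list-invited children. Take the list-invited prevalence as the true value. Then pooled/true = (1-f) + f x RR = 1 + f(RR-1). The documents give neither f nor RR, so every entry is an assumption.

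| f | RR 0.5 | RR 1 | RR 1.5 | RR 2 | RR 3 |
|---|---|---|---|---|---|
| 10% | 0.95 | 1.00 | 1.05 | 1.10 | 1.20 |
| 30% | 0.85 | 1.00 | 1.15 | 1.30 | 1.60 |
| 40% | 0.80 | 1.00 | 1.20 | 1.40 | 1.80 |

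**4. Comparison with sampling error.** Half-width = 1.96 x sqrt(p(1-p)/n), ignoring family clustering.

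- Assumed p = 2%, n = 1300: 1.96 x sqrt(0.02 x 0.98/1300) = 0.76 points. At f = 30% and RR = 2 the pooled value is 2.0% x 1.30 = 2.6%, a shift of 0.6 points.
- p = 5%, n = 1300: 1.2 points. The same f and RR give 6.5%, a shift of 1.5 points. The 5% is the low end of the protocol's seropositivity range, not a stage prevalence.

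When f and RR are both material, the shift is about as large as the sampling error. When either is small, it is not.

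**5. List-invited families also select themselves.** At the planned 70% uptake, suppose participants have 5% prevalence and decliners 5%/r. Prevalence in all listed families is 0.7 x 5% + 0.3 x 5%/r, which is 5.0%, 4.5%, 4.25% and 4.0% for r = 1, 1.5, 2 and 3. Separating the routes does not remove this.

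**The case against.** The case on the other side has several parts.

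- **The population is defined elsewhere.** The abstract and Study Design and Setting name children, the age range and the centre, and give a reason for excluding non-Saudi children. The study is a pilot. The objective can be read as shorthand for that population. This stands as far as the exclusions go: they are disclosed design choices. It does not supply the missing limitation, and the objective is the sentence against which the result will be reported.
- **Bias is not shown.** A reader might infer that the prevalence is inflated, or that it is inflated by a known amount. The documents do not support either. They give no mix of routes and no prevalence by route. RR could be 1 or below 1. Symptom-driven referral would bear mainly on stage 3 and has no obvious effect on stage 1. The symptom check applies to every participant, not only to self-referred children.
- **Outside families are a contingency.** A reader might count them as a fixed part of the sample. They are not, and on the protocol's figures their share is 0-1%.
- **Responders to advertisements may be families of the centre.** Some may already be on the lists, so f has no anchor in the text. This stands, and it is a reason to record the route.
- **A split by route may be planned.** A reader might conclude that one pooled percentage is fixed. The article states no strata, but a full protocol or analysis plan that is not shown could contain them. The lack of a split is therefore not an error in itself. No analysis plan, however, can make a sample of children from one centre represent all relatives nationally.

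**Conclusion.** The concern holds in a limited form. The mismatch between the national wording of a primary objective and a single-centre, children-only, partly self-referred sample is in the text and needs no assumption. So is the gap in the limitations, which leave out single-centre and volunteer selection and count the mix of recruitment strategies as help with generalizability.

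From this it follows that the stage prevalence is open to selection bias, not that it is biased. Size and direction are unknown. The illustration runs from no effect at RR = 1 to +30% at an assumed f = 30% and RR = 2, and falls below the true value if RR is under 1. The exposure is most plausible for stage 3. The point does not depend on outside families being recruited.

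**What to change.** 1. Restate the objective and the conclusion as prevalence in screened Saudi children aged 2-18 who have a first-degree relative with T1D and were recruited through this Riyadh centre.
2. Record the recruitment route for each family: invited from the KSUMC lists, self-referred, or outside the UDC. Identify self-referred families who are also on the lists.
3. Report stage prevalence for list-invited families, with their participation rate, separately from self-referred and any outside families, beside the pooled figure.
4. Show stage 3 prevalence with and without children who had symptoms at enrollment.
5. Add single-centre and volunteer selection to the limitations.

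**Cost.** One data field, some wording, and less precision for the list-invited estimate. If 30% are self-referred, n falls from 1300 to 0.70 x 1300 = 910, and at an assumed 2% prevalence the 95% half-width goes from 0.76 points to 1.96 x sqrt(0.02 x 0.98/910) = 0.91 points, ignoring family clustering. Total enrollment is unchanged. Non-response among listed families remains, which is why their participation rate belongs beside the estimate. Route is best recorded at enrollment, since recovering it later may be unreliable.

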#### Secondary Objectives

The secondary objectives are as follows:

Examine the psychological impacts of T1D screening on caregivers, including changes in anxiety, depression, distress level, and health-related quality of life before and after receiving screening results.Evaluate the effect of early detection on reducing DKA incidence at stage-3 T1D onset.Analyze the cost-effectiveness of implementing a T1D-screening program in Saudi Arabia.Evaluate the natural history of T1D progression in identified presymptomatic individuals, tracking time to clinical onset and changes in health outcomes over time.Examine the effectiveness of educational interventions on caregivers’ knowledge of T1D screening and early identification.Investigate the genetic predisposition to T1D within our population through human leukocyte antigen (HLA) testing and validate the genetic risk score (GRS) 2 in the Saudi population.

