#### Phase 1: T1D Screening

Families are recruited and scheduled for an enrollment and screening visit, where they receive comprehensive counseling about participation and education on T1D screening. Upon obtaining informed consent and assent, participants undergo baseline assessments, including completion of questionnaires and the collection of blood samples for islet autoantibody testing. Optional genetic screening for HLA phenotyping and GRS analysis is also offered to evaluate genetic predisposition to T1D. To enhance recruitment, a home testing option is provided, allowing families to conveniently perform finger-prick testing and data collection at home.

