##### Genetic Risk Screening

This pilot study integrated optional HLA phenotyping and GRS testing to deepen the understanding of T1D pathogenesis in the Saudi population. Analyses will be conducted by Enable Biosciences, the Barbara Davis Center for Childhood Diabetes, and delegates [28,29]. These tests are used for research purposes only.

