###### GRS Testing

The GRS aggregates the cumulative contribution of multiple genetic variants into a single score estimating an individual’s genetic predisposition to T1D [29,31-33]. This study uses GRS2, an advanced version that incorporates HLA haplotypes, non-HLA loci, and interactions between HLA variants [34]. Testing is conducted using a Kompetitive allele-specific polymerase chain reaction (PCR) assay, as described earlier [35,36]. The Kompetitive allele-specific PCR assay is a cost-effective and efficient alternative to the traditional DNA array and imputation-based methods. It successfully genotypes 60 of the 67 single nucleotide polymorphisms in GRS2, with the remaining single nucleotide polymorphisms excluded due to genotyping challenges. This study represents one of the first applications of GRS2 in FDRs of patients with T1D and the first validation of its use within the Saudi population.

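### The GRS2 objective claims validation in the Saudi population, but the sample described as genotyped supports only an estimate among Saudi first-degree relatives who opt in

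*Protocol article*

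**What the plan says.** The last secondary objective is to study HLA-related predisposition and to "validate the genetic risk score (GRS) 2 in the Saudi population". The GRS Testing section presents the study as an early use of GRS2 in FDRs and, as a separate item, as "the first validation of its use within the Saudi population".

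The rest of the protocol article describes who supplies the genetic data:

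- **Enrolment** (Study Design and Setting): Saudi children aged 2-18 years with an affected FDR. "Participants are recruited from the University Diabetes Centre (UDC) at King Saud University Medical City (KSUMC) in Riyadh, Saudi Arabia". Under Sample Size, any widening of recruitment is again to FDRs.
- **Genotyping**: "Optional genetic screening for HLA phenotyping and GRS analysis is also offered to evaluate genetic predisposition to T1D" (Phase 1: T1D Screening). Genetic Risk Screening also calls it optional. Expected uptake is not given.
- **Index cases** (Demographics and Clinical Characteristics): questionnaire data only.
- **Controls** (Statistical Analysis): the only controls mentioned are people with stage-3 T1D, used in the cost-effectiveness ratio. They are not said to be genotyped.
- **Analysis of the score** (Statistical Analysis): one covariate in a Cox model of progression among participants with presymptomatic T1D.
- **Version of the score** (GRS Testing): "It successfully genotypes 60 of the 67 single nucleotide polymorphisms in GRS2"; the reason for leaving out the rest is given.

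**The concern.** Validating a risk score in a population means showing how it is distributed there, how well it separates people with the disease from people without it, and whether the risks or cut-offs attached to it hold. All three refer to the population named. Here that population is Saudis in general, while the people typed are relatives of cases, who carry more risk alleles than unrelated Saudis do.

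The protocol recognises the difference. The Background puts the lifetime risk of FDRs at 15 times that of the general population. Genetic Testing Disclosure cites both that elevated risk and the absence of validated Saudi population-based estimates as reasons to restrict disclosure.

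What is at stake is how the result will be read. The pilot is meant to inform a national, population-based programme (Abstract, Conclusions), and the outcome definitions include a category of isolated genetic predisposition based on positive genetic markers. A score distribution or threshold from opt-in relatives, published as a Saudi validation, could be taken as a population reference. The limitations paragraph of the Discussion ties the FDR restriction to the acceptability of screening and does not extend it to the genetic claim.

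**Working it through.** **1. What each quantity needs, and what the described sample supplies.**

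| Quantity | Needs | Available as described? |
|---|---|---|
| Saudi population score distribution and cut-offs | Unrelated, unselected Saudis typed | No |
| Case-versus-unrelated discrimination | Typed Saudi cases and unrelated Saudi controls | No |
| Calibration of population risk | Typed population sample with outcomes | No |
| Discrimination for autoantibody positivity among FDRs | Typed FDRs, positive and negative | Yes, in those who opt in |
| Association with progression among FDRs | Typed autoantibody-positive FDRs, followed up | Yes; the Cox model covers presymptomatic participants |

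The first three rows are what a claim about the Saudi population implies. The last two are what the study can deliver.

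**2. Is there a sample-size figure to reproduce?** Not for this objective. The only target is 1300 participants in 322 families, which is a recruitment count: 0.70 × 460 = 322 (the clinic cohort is given as 450-500), and 1300/322 = 4.04 children per family.

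**3. Precision of the achievable estimate (illustration).** Inputs: 1300 participants and 5-15% seropositivity (Sample Size). Assumptions: 50% uptake and an AUC of 0.70.

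- Genotyped: 1300 × 0.50 = 650.
- Seropositive: 650 × 0.05 = 32.5, or 650 × 0.15 = 97.5. Seronegative: 617.5 or 552.5.

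Hanley-McNeil: SE² = [A(1−A) + (n1−1)(Q1−A²) + (n0−1)(Q2−A²)]/(n1·n0), with Q1 = A/(2−A) = 0.70/1.30 = 0.5385 and Q2 = 2A²/(1+A) = 0.98/1.70 = 0.5765.

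- At 5%: (0.21 + 31.5 × 0.0485 + 616.5 × 0.0865)/(32.5 × 617.5) = 0.00274; SE = 0.052; 1.96 × SE = 0.103.
- At 15%: (0.21 + 96.5 × 0.0485 + 551.5 × 0.0865)/(97.5 × 552.5) = 0.00098; SE = 0.031; 1.96 × SE = 0.061.

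The half-width is therefore about 0.06 to 0.10. Because uptake is not stated, the range matters: at 25% uptake it is 0.087 to 0.145, and at 100% it is 0.043 to 0.073. If half of the seropositive children had multiple autoantibodies (a further assumption), the half-width for that outcome at 50% uptake would be about 0.08 to 0.15. With about four children per family, sibling correlation would widen all of these.

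**The case against.** **Population may mean ancestry.** Non-Saudi children are excluded because of differing ethnic and genetic backgrounds, so the term is partly about ancestry, and testing a score in relatives of that ancestry is a form of external validation. This has weight. But the GRS Testing section names use in FDRs and validation in the Saudi population as two separate achievements, and Genetic Testing Disclosure treats a Saudi population-based estimate as something still lacking.

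**The article is condensed.** The full protocol or analysis plan may describe an AUC analysis or an external reference sample. That is fair, and the lack of analysis detail is not the point. The article makes the claim twice and describes a tested group that does not match it.

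**Little harm follows.** Genetic tests are for research only, results are shared only on request, and nothing says that score cut-offs from this study will be used nationally. This stands and limits the weight of the point.

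**Stronger readings that the documents do not support:**

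- *Discrimination will look poor in relatives.* With normal scores, equal SDs and the relatives' mean halfway between population and cases, Φ(d/(2√2)) with d = √2·z(AUC) turns population AUCs of 0.80-0.92 into 0.66-0.76. That formula compares population cases with relatives, a contrast this study does not run. A simulation of affected versus unaffected people within relatives (assumed: sibling score correlation 0.5, logistic risk, 0.4% baseline risk, T1D as outcome) gave about 0.80, 0.85, 0.89 and 0.90 for population AUCs of 0.80, 0.85, 0.90 and 0.92. No large fall can be predicted, and a weak AUC is not to be expected merely because the sample consists of relatives.
- *No case is genotyped.* This is too absolute. A few participants may have stage 3 at screening or reach it in follow-up. They are all FDRs and give no population comparison.
- *The 60-SNP version is an error.* It is disclosed with its reason. It matters only in that the result should be labelled as belonging to that version.

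**Conclusion.** The mismatch is real, and it is one of scope. The sample described supports statements about the 60-SNP GRS2 among Saudi FDRs who accept genotyping. It does not support a Saudi population distribution, cut-offs, calibration or case-versus-unrelated discrimination. This conclusion rests on who the article says is typed and needs no numerical assumption. It would change only if the full protocol describes genotyped Saudi cases and unrelated Saudi controls.

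No plan figure is wrong here. The precision of about ±0.06 to ±0.10 depends on the assumed 50% uptake and AUC of 0.70, and it ignores clustering. It shows that the narrower aim is workable, with moderate precision. The point is minor to moderate: it concerns one secondary, research-only objective and touches neither primary objective.

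**What to change.** In the Secondary Objectives and in GRS Testing, replace the validation claim with: *estimate the discrimination of the 60-SNP GRS2 for islet autoantibody positivity (any; multiple) among Saudi first-degree relatives who accept genotyping*. Report it as an AUC with a 95% confidence interval clustered by family, and give uptake of genotyping by antibody status so that readers can judge selection. Drop the words on validation in the Saudi population.

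The cost is two edits and one pre-stated analysis, with no new samples. The downside is a more modest claim. Keeping the population claim would instead require genotyped Saudi cases and unrelated Saudi controls, which is a larger undertaking than this pilot describes.
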